### Dropout and follow-up

In case of emergencies (like severe increase of symptoms, suicidality) deviation from the protocol is allowed. Subjects can leave the study at any time for any reason if they wish to do so. The researcher can — in consultation with the group therapists — also decide to withdraw a subject from the study for urgent medical or psychological reasons. Reasons for dropout or withdrawal will be registered. Patients who withdraw from treatment will also be asked to complete follow-up assessments. As mentioned before, during the active treatment phase, participation in other treatments, starting medication or raising the medication dosage is not allowed. Also missing too many sessions is not permitted (patients should at least attend a minimum of 80 % of the sessions); if too many are missed, treatment will be terminated (pushout). In consultation with the patient, taking into account the reason for dropout, a suitable alternative will be discussed.

The follow-up period is experimental for the first 3 months (patients are not provided additional treatment unless clinically deemed necessary, e.g. in case of crisis). After this period, patients are offered an appointment with one of the group therapists. Depending on the wish of the patient, main treatment results and further treatment needs can be discussed. From then on follow-up will be naturalistic, meaning that patients are free to seek help in case of unsatisfactory treatment results and/or additional need for treatment.

### Instruments

The measures described below will be administered on different measurement occasions. At all time points self-report measures will be conducted online, except for the AQ and pre-screener of the SCID-II used in the inclusion and exclusion procedure (see inclusion procedure above). On request, participants can complete the self-report measures on paper.

The administration of the SCID-II and the MINI during the intake phase will be conducted face to face. At the last assessment (T5) patients can choose between a face-to-face or telephone administration of the SCID-II, APD section and the MINI, SAD section, according to their preference. For practical reasons, all AVPDSI assessments are administered by phone. Research supports the validity of structured telephone interviews for data collection from primary care patients [35]. See Fig. 1 for the exact measurements per occasion. To ensure privacy of participants and safe data storage, data will be entered in a data file anonymously; participants will be given a unique number, and only the research assistant will be able to link the number with the name of the patient. Data will be stored on a laptop used only for research purposes, and a salted and encrypted file server which has been advised by an independent tech consultant.

### Primary outcome measures

The primary outcome measure for severity of social anxiety is the *self-report version of the Liebowitz Social Anxiety Scale (LSAS-SR).* The objective of the LSAS [36] is to assess the range of social interaction and performance in situations which patients with SAD may fear. The scale contains two parts: one part measures the level of anxiety, and the other part measures the level of avoidance. It consists of 24 items, 13 relating to performance anxiety and 11 concerning anxiety in social situations [37]. The LSAS was originally developed as a clinician-administered semi-structured interview. The LSAS self-report version has comparably good psychometric properties (convergent and discriminant validity, internal consistency, test-retest reliability, criterion validity), high correlation with the clinician-administered version and sensitivity to treatment change. Furthermore, the self-report version is easier to administer and is less time-consuming for both patient and clinician [38–40]. The LSAS-SR will be administered at all time points, i.e. at the start, halfway and at the end of the treatment period and during follow-up at 3, 6 and 12 months after study treatment (see Fig. 1).

The primary outcome measure for severity of APD is *the clinician-administered Avoidant Personality Disorder Severity Index (AVPDSI).* The AVPDSI is a semi-structured interview developed specifically for this study to assess the frequency and severity of manifestations of APD, as defined in the DSM-IV/5, during the last month. The purpose of this instrument is to yield a quantitative index of the current severity of APD manifestations, in terms of both avoidance and fear. The AVPDSI is modelled after the Borderline Personality Disorder Severity Index (BPDSI), which was originally developed by Weaver and Clum [41] and further developed and validated in Dutch by Arntz et al. [42] and Giesen-Bloo et al. [43]. The information gathered by the AVPDSI in the context of the RCT will also be used in a larger study in which the psychometric properties of the interview will be assessed. To ensure quality of data collection of this newly developed instrument, a training protocol will be developed and all measurements will be audiotaped. A random selection of tapes will be listened to in order to assess interrater reliability. This semi-structured interview will be conducted before the start of treatment and at 3 and 12 months follow-up (see Fig. 1).

### Secondary study parameters

#### Mini-International Neuropsychiatric Interview (MINI), social anxiety disorder section

The presence of SAD will be assessed with this section of the MINI [44, 45] as a part of the inclusion procedure and at 12 months follow-up (see Fig. 1). The validation of the Dutch translation of the clinician rated (CR) version of the MINI [46] against the Structured Clinical Interview DSM-III-R-patient version (SCID-P) and the Composite International Diagnostic Interview for ICD-10 (CIDI) showed good to very good kappa values [45].

#### Structured Clinical Interview for DSM Axis II Disorders (SCID-II), APD section

The APD section of SCID-II will be used to assess the presence of APD during inclusion and 12 months after treatment (see Fig. 1). Studies found adequate to good interrater reliability for SCID-II interviews [47–49].

#### Schema Mode Inventory 2 (SMI-2)

The SMI-2 [23] is a modified version of the SMI-1 [50] and successfully distinguishes between patients and controls. Newly formulated modes proved to be appropriate for histrionic, avoidant and dependent personality disorder. The results supported recent theoretical developments in schema therapy (ST). The questionnaire is useful for application in clinical practice. Questions from the SMI-1 [50] concerning the happy child mode were added to the SMI-2 because of its putative therapeutic relevance in the ST treatment for patients with APD.

#### Inventory of Depressive Symptomatology Self-Report (IDS-SR)

Depressive symptomatology is measured by the IDS-SR [51], which encompasses all the relevant symptoms for major depressive disorder based on the DSM-IV [2]. It consists of 30 items, with total scores ranging from 0–84 (only 28 of the 30 items are rated, with each item rated 0–3) [52]. The questionnaire has highly acceptable psychometric properties with reasonable internal consistency, interrater reliability and concurrent and discriminant validity and is a sensitive measure of symptom severity in depression [51, 53]. The self-report version is as sensitive to change as the clinician-administered version [52].

#### World Health Organization Quality of Life–BREF (WHOQOL-BREF)

The WHOQOL-BREF [54] was developed as an international cross-culturally comparable self-report quality of life assessment instrument. It assesses the individual’s perceptions of quality of life in the context of their culture and value systems, personal goals, standards and concerns across four domains: physical health, psychological health, social relationships and environment. The internal consistency of the four domains of the WHOQOL-BREF ranged from 0.66 to 0.80. Domain scores of the WHOQOL-BREF correlated around 0.92 with the WHOQOL-100 domain scores. Relatively low correlations were found between demographic characteristics (age and sex) and WHOQOL-BREF domain scores. It is concluded that the content validity, construct validity and the reliability of the WHOQOL-BREF in a population of adult Dutch psychiatric outpatients are good [54].

#### Difficulties in Emotion Regulation Scale (DERS)

The DERS [55] is a 36-item self-report questionnaire consisting of six subscales: (1) Non-acceptance of emotional responses (6 items); (2) Difficulties engaging in goal-directed behavior (5 items); (3) Impulse control difficulties (6 items); (4) Lack of emotional awareness (6 items); (5) Limited access to emotion regulation strategies (8 items); (6) Lack of emotional clarity (5 items). The internal consistency for the total scale as well as for the subscales appeared to be adequate (varying between a Cronbach’s alpha of 0.80 and 0.93). The questionnaire also has adequate construct and predictive validity and good test-retest reliability.

#### The Rosenberg Self-Esteem Scale (RSES)

The RSES will be used to assess self-esteem. It is a widely used 10-item Likert scale self-esteem measure. Items are answered on a 4-point scale — from strongly agree to strongly disagree — measuring positive and negative feelings towards the self [56]. The Dutch version of the RSES is found to be a one-dimensional scale with high internal consistency and congruent validity and a Cronbach’s alpha of 0.89 [57].

#### Acceptance and Action Questionnaire (AAQ-II)

The AAQ-II [58] is a self-report measure designed to assess experiential avoidance. It consists of 10 items which are scored on a Likert scale from 1 to 7 with total scores that vary from 10 to 70. Higher scores are indicative of more acceptance and less experiential avoidance. It appears to be a unidimensional measure with sound factor structure and good reliability and validity. The mean alpha coefficient is .84 and the 3- and 12-month test-retest reliability scores are .81 and .79 respectively [58]. Construct validity, internal consistency, convergent and divergent validity of the Dutch version are comparable with the English version [59].

#### Childhood Trauma Questionnaire-Short Form (CTQ-SF)

The aforementioned questionnaires SMI-2, IDS-SR, WHOQOL-BREF, DERS, RSES and AAQ-II are conducted at all time points (see Fig. 1). In addition to outcome measures, information on sociodemographic and clinical history variables will be collected at baseline. To assess childhood trauma, the CTQ short form [60] is chosen. The short form was developed from the original version of the CTQ which has 70 items [61]. Because of its brevity of administration and assessment of multiple types of maltreatment, it is well suited for treatment studies like this RCT. The short form consists of 28 items measuring physical, sexual and emotional abuse and physical and emotional neglect, and its reliability and criterion-related validity have been established [60]. A recent study in the Netherlands among a large sample of participants (2308) with or without a current depressive and/or anxiety disorder concludes that the five-factor model fits the data well, that the total scores represent a broad dimension of maltreatment during childhood and that the factorial validity and reliability data make it a good instrument for various forms of abuse and neglect in childhood in clinical settings [62].

### Screening instruments

In the inclusion procedure the MINI and the SCID-II, which are both described above, are used to assess respectively Axis I and II disorders. In addition, patients are screened with the Autism-Spectrum Quotient (AQ).

#### Autism-Spectrum Quotient (AQ)

Since the presence of an autism spectrum disorder (ASD) requests a highly specific treatment and patients with an ASD would probably not benefit from the treatments offered in the RCT, it was decided to exclude patients with a score exceeding the clinical cut-off score on the Autism-Spectrum Quotient (AQ). Patients who score above the cut-off are offered referral for full diagnostic assessment. The AQ is a short self-administered scale for identifying the degree to which any individual adult of normal IQ may have autistic traits. Individuals score in the range 0–50. The higher the score, the more autistic traits a person possesses [27, 63] with a cut-off of 32 for distinguishing individuals with clinically significant levels of autistic traits [27]. The AQ comprises 50 questions assessing five different areas: social skill, attention switch, attention to detail, communication and imagination. It has reasonable construct and face validity and good test-retest and interrater reliability [27] and is a useful screening instrument in clinical practice [64]. The Dutch translation has been shown to be a reliable instrument to assess autism spectrum condition (ASC) traits and has satisfactory internal consistency and test-retest reliability. High total AQ scores are specific to patients with an ASD and set them apart from both the general population and from patients with SAD [65].

### Statistical analysis

Pre-test differences between both treatment groups and between treatment completers and dropouts will be calculated by means of independent *t* tests, nonparametric tests or chi-square tests when appropriate. Multilevel analysis (MLA) will be used to investigate the effectiveness of GCBT and GST in reducing social anxiety symptoms and manifestations of AVPD, and the secondary outcomes. MLA is especially suitable to analyse repeated measure data because it takes into account the dependencies among observations nested within individuals. Another advantage of this methodology is its ability to handle missing data, a problem often occurring in longitudinal research [66]. The data has a three-level hierarchical (multilevel) structure: repeated measures at the first level, individuals at the second level, treatment condition at the third level. For dimensional outcomes the appropriate underlying distribution (e.g. normal, gamma, negative binomial) will be determined based on the observed distributions of residuals. For the repeated part, the best fitting covariance structure will be determined empirically. Moreover, multilevel logistic regression analysis will be performed in order to investigate whether GCBT compared to GST results in a higher proportion of remitted APD. Survival analysis will be used to compare conditions in treatment retention. The identification of possible predictors, moderators and mediators will be based upon the recommendations of Kraemer [25]. Linear regression methods will be applied to identify predictors/moderators related to treatment outcome. Bootstrapping methods [67] will be used to investigate the mediating effects of, for example, emotion regulation on symptom reduction. Furthermore, effect sizes and clinical significant change according to the Jacobson and Truax criteria [68] will be calculated to estimate respectively the magnitude of the treatment effect and the significance of the results for clinical practice.

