## Methods/design

### Design

The design of the study will be a 30-session (on a weekly basis), two-group (GST, GCBT) randomized controlled clinical trial with repeated measurements at baseline (T0), mid-test (T1), post-test (T2) and at 3 months follow-up (T3), half-year follow-up (T4) and 1-year follow-up (T5). Assessment will include diagnostic interviews, symptom questionnaires and quality of life, self-esteem, schema-related and emotion regulation measures. See Fig. 1 (Flow chart of enrolment, intervention and assessments) and Additional file 1 (Standard Protocol Items: Recommendations for Interventional Trials (SPIRIT) flow diagram) for an overview of the study; the SPIRIT checklist is presented in Additional file 2. Diagnostic interviews are based on the DSM-IV classification system [2], since the DSM-5 [8] was not yet available during the developmental phase of this study and there was an absence of diagnostic instruments based on the DSM-5 at the start of the study.

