### Population/sample size

Before the start of the randomized controlled trial (RCT), a chart review showed that both the PsyQ location of Rotterdam and the PsyQ location of The Hague have an annual patient flow of 40 patients with both SAD as well as a comorbid APD. This represents an overall yearly *N* of 80, of which it is expected that approximately 90 % (*N* = 72) will be included. This means that every year in each department 36 patients can be randomized over the two conditions. CBT and ST groups consist of a maximum of 9 patients.

We know that CBT has a large effect on SAD compared to waitlist and a small to moderate effect compared to placebo [15]. With respect to ST, in a randomized trial comparing ST, clarification therapy and treatment as usual (TAU), Bamelis et al. [19] found an odds ratio between ST and TAU in recovery from PD diagnosis in the 3–4 range (depending on the specific (sensitivity) analysis), which is equivalent to Cohen’s *d* = .60–.76 [26]. Though a substantial number of patients in the ST condition had a diagnosis of APD, only a small minority of patients received CBT as TAU. No studies are available directly comparing ST with CBT with respect to APD with comorbid SAD. We therefore designed our RCT as a superiority trial with enough statistical power to detect a difference in outcome between treatments (if present) with a medium effect size (Cohen’s *d* = .5). We chose this minimum difference because such a difference is important based on a patient’s perspective or clinical knowledge. Expecting larger differences in outcome does not seem realistic and might result in an underpowered study, while detecting smaller differences is of less relevance for clinical practice. Thus, we designed our study to detect a medium effect size (0.50) with a power of 80 % and a two-tailed alpha set at 0.05 on the primary outcome measures, severity of social anxiety (Liebowitz Social Anxiety Scale Self-Report, LSAS-SR) and severity of avoidant personality disorder (Avoidant Personality Disorder Severity Index, AVPDSI). This implies that 64 patients per study group and in total 128 patients are needed for the present project.

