### Interventions

Different guidelines recommend CBT for treatment of SAD [28–30]. CBT is seen as the gold standard for SAD with respect to non-pharmacological treatment, and gains achieved with CBT seem to persist longer than those achieved with pharmacotherapy [29]. Guidelines differ with respect to the advised treatment format (individual or group therapy). The Canadian guidelines do not express any preference, NICE guidelines advise individual CBT and Dutch guidelines recommend group CBT [28–30]. None of these guidelines advises on the treatment of SAD and comorbid APD. With respect to APD, guidelines are scarce. Dutch multidisciplinary guidelines recommend group behavioral treatment for patients with APD. They specify that in case of comorbidity of SAD and APD, CBT is seen as an adequate treatment option, although prolonged treatment is necessary to realize comparable favourable outcomes as for SAD only [13].

GCBT is a regular treatment option and fits neatly in the health care program offered at the RCT participating departments of anxiety disorders. GST will be a new treatment, but will be performed by skilled and experienced therapists. Both treatments were piloted in advance to enable therapists to become acquainted with the treatment protocol and the semi-open group format. In the ST condition therapists had no former experience with ST in a group format; therefore, this treatment modality was permitted an 8 months longer pilot period. In The Hague the pilot period for GST was 18 months and for GCBT 10 months. In Rotterdam the pilot period for GST took 32 months and for GCBT 24 months, this was due to a major reorganisation. 

For patients of both GST and GCBT, treatment comprises of 30 weekly group sessions of 90 minutes, preceded by 2 introductory individual sessions of 45 minutes. In addition to the group treatment, limited individual time with the therapist is permitted with a maximum of 180 minutes. Individual contact can take place in person or by phone or e-mail and can be initiated by either patient or therapist, for instance if urgent personal matters come up or if the therapist fears dropout and wants to discuss possible obstacles for the patient. Sessions will be audiotaped to assess protocol adherence. For both GST and GCBT, customized rating forms will be developed and a random selection of tapes will be listened to in order to evaluate to what extent therapists adhere to the protocol.

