### Group schema therapy (GST)

GST is a recently developed treatment for personality disorders. GST is shorter, more directive, confrontational and integrative — using experiential, cognitive and behavioral techniques, addressing childhood and present — than traditional psychodynamic psychotherapies for personality disorders. Schemas can be described as psychological constructs that include beliefs that we have about ourselves, the world and other people, which result from interactions of innate temperament and early environmental factors, notably trauma and unmet core childhood needs. When maladaptive schemas are triggered, specific states occur, as the result of the combination of activated schema(s) and type of coping, that can be described as schema modes. Schema modes are central in GST. Schema modes often had an adaptive role in childhood (e.g. in terms of survival in an adverse situation), but become maladaptive and limiting in adulthood. GST aims at reducing the use of dysfunctional coping modes, healing the maladaptive child modes, banishing the internalized parent modes and strengthening the adaptive modes (healthy adult mode and happy child mode). The ultimate goal of GST is to enable patients to get their emotional needs met, including gaining autonomy and forming healthy social relationships. In GST the group is used as an analogue for the family of origin with the other group members as ’siblings’ and the therapists as ’parents’. Group processes can be used to create corrective emotional experiences and to reduce maladaptive coping modes [24].

For this study, a 30-session treatment protocol of 90-minute weekly sessions over 9 months was developed. The treatment protocol is naturalistic in the sense that, apart from the framework directing treatment focus throughout sessions, therapists do not have a session-to session detailed treatment manual. The structure of the group will be semi-open, and every 10 weeks new patients can enter an ongoing group. Before a patient enters the group, two individual meetings will be planned to provide some information about the content and the process of GST, to discuss briefly the results of the Schema Mode Inventory (SMI) and to formulate a case conceptualization in schema mode terms in collaboration with the patient.

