Participants are encouraged to engage in homework between sessions to gain corrective experiences in line with individual needs. Thus, homework does not focus on exposure to social situations that are feared, but on finding ways to better meet one’s needs. Each course will be provided by two experienced therapists who received formal GST training by [name]. They will receive monthly supervision (1.5–2 hours) by [name] using Skype.

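### The three-level model puts treatment condition where the therapy group belongs, so clustering within therapy groups goes unmodelled on both primary outcomes

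*Protocol article*

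**What the plan says.** The Design section describes a "two-group (GST, GCBT) randomized controlled clinical trial with repeated measurements". Under Statistical analysis, "Multilevel analysis (MLA) will be used to investigate the effectiveness of GCBT and GST" on social anxiety, on avoidant personality disorder and on the secondary outcomes. The section gives a complete three-level hierarchy: "repeated measures at the first level, individuals at the second level, treatment condition at the third level". The method is justified because "it takes into account the dependencies among observations nested within individuals"; no other dependence is mentioned.

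Treatment itself is delivered in groups. In both arms, according to the Interventions section, "treatment comprises of 30 weekly group sessions of 90 minutes". The Population/sample size section adds that "CBT and ST groups consist of a maximum of 9 patients". For group schema therapy (GST), "Each course will be provided by two experienced therapists" and "every 10 weeks new patients can enter an ongoing group". The section on group cognitive behavioral therapy (GCBT) gives the same entry interval and also two therapists per course. Nowhere does the article name therapy group, therapist pair or site as a level, random effect or covariate.

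**The concern.** Two things are wrong with the stated hierarchy.

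First, condition has two categories, both of direct interest. It belongs in the fixed part of the model, with time and their interaction. It is not a sample of units whose variance one would estimate.

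Second, the unit that does create dependence between patients is absent. Members of a therapy group share sessions and therapists, and the article counts on the group as an ingredient of treatment: the GST section relies on group processes, and the GCBT section on learning from fellow members. Each therapy group delivers only one treatment, so groups are nested within arm, and any variation between groups falls directly on the GST versus GCBT comparison. A model that knows only about repeated measures within patients will understate the standard error of that comparison. At stake is the 0.05 error rate on both primary outcomes, and with it the power claim.

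**Working it through.** **Inputs from the article.** d = 0.50, power 80%, two-sided alpha 0.05, 64 per arm and 128 in total, groups of at most 9 (Population/sample size).

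**Assumed.** The ICC, which the documents do not give: 0.02, 0.05 and 0.10. It refers to the outcome as analysed, that is, after allowing for baseline. An average group size m of 6 is taken as an alternative, because 9 is a ceiling.

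**The plan's own figure.** A two-sample t test at d = 0.50 needs 63.77, so 64 per arm, with 80.1% power. The 64 reproduces, as a formula for independent patients with no allowance for clustering.

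**Type I error when groups are ignored.** Design effect DE = 1 + (m − 1) × ICC. Actual two-sided error = 2 × [1 − Φ(1.96 / √DE)].

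| m | ICC | DE | 1.96/√DE | Actual error |
|---|---|---|---|---|
| 9 | 0.02 | 1.16 | 1.82 | 6.9% |
| 9 | 0.05 | 1.40 | 1.66 | 9.8% |
| 9 | 0.10 | 1.80 | 1.46 | 14.4% |
| 6 | 0.02 | 1.10 | 1.87 | 6.2% |
| 6 | 0.05 | 1.25 | 1.75 | 8.0% |
| 6 | 0.10 | 1.50 | 1.60 | 11.0% |

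A simulation of 20,000 trials, with seven groups of 9 and a remainder of 1 per arm and an ordinary t test, gave 10.1% at ICC 0.05 and 14.1% at ICC 0.10, in line with the formula.

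**Power at 64 per arm once groups are modelled (m = 9).** Noncentrality = 0.5 / √(2 × DE / 64). Between-group degrees of freedom = 2 × (64/9 − 1) ≈ 12.

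| ICC | Noncentrality | Power, t with about 12 df | Power, normal approximation |
|---|---|---|---|
| 0.02 | 2.63 | 67.6% | 74.7% |
| 0.05 | 2.39 | 59.5% | 66.7% |
| 0.10 | 2.11 | 49.3% | 55.9% |

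**Is a group intercept enough?** Baseline measures are completed before randomization (Inclusion and exclusion procedure and randomization), so a group can influence its members only afterwards. Write a patient's baseline score as a + e0 and the later score as a + v + e1, where v is the effect of the group. The change is v + e1 − e0, so v stays in the treatment × time contrast. A group random intercept enters both scores equally and cancels from the change. In balanced pre-post data it therefore leaves the standard error of treatment × time uncorrected. A small simulation agrees: 14 groups of 9, a group effect only after baseline, ICC 0.10, 400 null trials. The rejection rate was 13.5% (54 of 400) both with a group intercept and with a change-score test that ignored groups. Many of those fits gave convergence warnings, so the argument rests on the algebra.

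**The case against.** The strongest reply is that the sentence describes the structure of the data and never calls condition random. The rest of the section treats condition as a contrast, in the logistic model for remission and in the survival comparison of retention, and the Background poses the research question as a comparison. The natural reading may be a between-patient predictor, loosely worded. This stands. A reader might infer that the model, fitted as written, gives no valid test of GST against GCBT, because a variance from two units has one degree of freedom and competes with the treatment effect. That would follow only if condition were specified as a random level, which the article does not say. The reply does not rescue the hierarchy, though: with condition read as a predictor, two levels remain and the therapy group is still absent.

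A second reply is that the analysis plan may settle the matter. An article may leave detail to that plan, but here it fills all three levels, and fills the third wrongly.

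A third is that the size of the harm is unknown and that semi-open membership blurs the clusters. The ICC is indeed assumed, and 9 is a maximum. Overlapping membership complicates the modelling but does not make patients independent.

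A reader might also take the cluster to be one continuously running group per arm and site, about 64/2 = 32 patients, and arrive at error rates of about 12% / 22% / 33%. The documents do not support that. They do not state how many groups run. The planned 36 patients per site per year means 18 per arm, more than the 9 × 52/30 = 15.6 that one group of 9 could take in. More centres may also be added. The formula would further assume equal correlation between patients who never share a session, although they may share therapists.

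**Conclusion.** The point holds as one about unmodelled therapy groups, together with a sentence that names the wrong third level. Whether condition was meant as a level or as a predictor, the stated structure ignores dependence within groups, and for any positive ICC the type I error on both primary outcomes exceeds 0.05. Over assumed ICCs of 0.02 to 0.10 it is about 7% to 14% with full groups of 9 and about 6% to 11% with an average of 6. The direction is certain once outcomes correlate within groups; the size depends on an ICC and an average group size that the documents do not give. The power claim shares the defect, because 64 per arm reproduces only for independent patients.

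**What to change.** Rewrite the sentence as repeated measures within patients within therapy groups, with treatment, time, treatment × time and site as fixed effects. Let the group-level random effect act on post-baseline change: a group × time term, a group random slope, or a group random effect in a baseline-adjusted model of the post-baseline scores. A group intercept alone is not enough. Use small-sample degrees of freedom, since groups are few. Record each patient's group and entry wave, so that the cluster can be defined despite entry every 10 weeks.

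The rewording is short, and the Trial status section reports recruitment as ongoing, so it can precede the analysis. The article does not say whether group membership is already recorded; if not, it must be collected. The real price is wider intervals and a weaker power statement. Population/sample size and the Discussion should say that 80% power for 128 patients holds only for independent patients, and should give power over a stated range of ICCs.
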